# Levonorgestrel-releasing intrauterine device plus metformin, or megestrol acetate plus metformin for fertility-sparing treatment of atypical endometrial hyperplasia and early endometrial carcinoma: a prospective, randomized, blind-endpoint design trial protocol

**DOI:** 10.1186/s12978-022-01513-8

**Published:** 2022-11-04

## Abstract

**Background:**

Endometrial adenocarcinoma (EC) is the fifth most common cancer in women worldwide, standard treatment for EC includes hysterectomy, but it results in the loss of reproductive function. Thus, conservative treatment for these patients is strongly demanded, progestin therapy is widely accepted as the main fertility-sparing treatment for young women with endometrial hyperplasia with atypia (EHA) and well-differentiated endometrioid endometrial cancer. This trial will investigate the effectiveness of conservative treatment for obese women with early-stage EC.

**Method and design:**

This will be an open-label, 2-armed, randomized, phase-II single-center trial of LNG-IUD plus metformin or megestrol acetate (MA) plus metformin. A total of 88 participants will be randomly assigned into 2 treatment arms in a 1:1 ratio. Clinical, laboratory, ultrasound and radiology data, will be collected at baseline, and then at 3, 6, 9, 12, 18, and 24 months. EC biomarkers will be collected at baseline. The primary aim is to determine the efficacy of a levonorgestrel-releasing intrauterine device (LNG-IUD) plus metformin, or megestrol acetate (MA) plus metformin in achieving pathological complete response (pCR) at 12 months, as well as post-treatment pregnancy outcomes and recurrence rate. The secondary aims are to predict the response to an LNG-IUD plus metformin and MA plus metformin via clinical, blood, and tissue predictive biomarkers.

**Conclusions:**

Prospective evidence for conservative treatment of EC is limited. New methods to achieve better CR rates with fewer side effects are needed. This trial will investigate the effectiveness of LNG-IUD plus metformin, and MA plus metformin, in obese women with early-stage EC, providing a non-surgical treatment option for these patients.

*Trial registration* ChiCTR2200055624. The trial was registered at http://www.chictr.org.cn/listbycreater.aspx on January 15, 2022

## Introduction

Endometrial adenocarcinoma (EC) is the fifth most common cancer in women worldwide [1]. Type 1 EC is typically associated with low-grade tumors with no or infiltrate the superficial muscularis, and with a good prognosis [2]. Endometrial hyperplasia with atypia (EHA) is a pre-malignant lesion of the endometrium, and is a precursor of endometrial cancer. Approximately 30% of women with complex atypical hyperplasia progress to endometrial cancer, and up to 40% of women diagnosed with complex atypical hyperplasia are found to have occult endometrial cancer at the time of hysterectomy [3, 4]. The current standard treatment for EC and EHA is total hysterectomy and bilateral salpingo-oophorectomy, with or without pelvic and para-aortic lymph node dissection [5]. For stage 1 EC, the 5-year disease-free survival (DFS) rate ranges from 80 to 95% [6]. Currently, many women delay childbearing and thus many premenopausal women without children are diagnosed with EC. However, surgical treatment can lead to loss of childbearing ability in women of childbearing age [7–18]. As such, effective non-surgical treatment is beneficial for this population.

Progestin therapy is widely regarded as the main fertility-sparing treatment for young women with EHA and early EC. It involves the use of the oral progestins medroxyprogesterone acetate (MPA) or megestrol acetate (MA), and more recently the placement of a levonorgestrel-releasing intrauterine device (LNG-IUD). Current recommendations are MPA at a dose of 400–600 mg/day or MA at a dose of 160–320 mg/day, with follow-up assessment of treatment response using dilation and curettage (D&C) and imaging studies. The LNG-IUD releases 52 mg of intrauterine progestin at a consistent rate for up to 5 years. MA is associated with higher remission rates compared to MPA and other hormonal treatments, possibly due to the relatively higher bioavailability of MA following oral administration compared to MPA [19]. Placing an LNG-IUD avoids patient noncompliance issues with oral medications and possible side effects associated with high-dose oral progestins [20].

Obesity, diabetes, and insulin resistance are considered risk factors for endometrial cancer. Obese patients also have a 2.5-fold increased risk of death from the disease as compared with non-obese patients [21]. High-dose progesterone is used to treat EHA and early-stage EC in women wishing to maintain fertility. However, high-dose progesterone treatment can lead to further weight gain, increased risk of thrombosis, and impaired liver function. High-dose progesterone is contraindicated if initial testing indicates abnormal liver function [22].

A study has shown that the addition of metformin to progesterone treatment improves the therapeutic effect of progesterone. A recent meta-analysis by Chae-Kim et al. including 6 studies and 621 women demonstrated that for reproductive-aged women with EHA or early-stage EC, the combination of a progestin and metformin is associated with a lower relapse rate, and similar remission, clinical pregnancy, and live birth rates as compared with progestin-alone treatment [23].

Metformin, an insulin sensitizer, is widely used in the treatment of type 2 diabetes and can reduce body weight and activate the AMPK pathway. Activation of the AMPK pathway affects metabolic functions and also inhibits the development of tumors [24, 25]. Clinical studies have shown that metformin exhibits antitumor effects [26, 27]. Schuler et al. conducted a window of opportunity study in which 20 EC women were treated with 850 mg metformin once daily for 1–4 weeks before hysterectomy. The results showed that the mean Ki-67 index (p < 0.008) was significantly decreased pre- to post-treatment [28]. Another study has shown that the expressions of estrogen receptors (ER) and progesterone receptors (PR) are significantly and positively correlated with the expressions of ERK1 and ERK2 in endometrial cancer [29]. These findings suggest that ERs and PRs may participate in the occurrence of EC via the ERK signaling pathway.

We hypothesized that metformin treatment can lead to prolonged PRs, even in the presence of progesterone, which would result in a more durable response to progesterone. In 2021, the feMMe trial (an open-label, randomized phase II clinical trial) demonstrated that the complete pathological endometrial remission rate was 61% for women treated with an LNG-IUD, 57% for women treated with an LNG-IUD plus metformin, and 67% for women treated with an LNG-IUD plus weight loss [30].

However, the outcomes of treatment with an LNG-IUD plus metformin, or MA plus metformin have not been compared. The primary aim of this phase II, 2-arm randomized trial is to determine the effectiveness of an LNG-IUD (Mirena®) plus metformin, and MA plus metformin to achieve a pathological complete response (pCR) at 12th months, pregnancy outcomes, and recurrence rates. The secondary aim is to predict the response to treatment with an LNG-IUD plus metformin, and MA plus metformin using clinical data and blood and tissue predictive biomarkers.

## Patients and methods

### Design

This trial is designed as an open-label, randomized phase II trial (Fig. 1). The study protocol was approved and registered by the Ethics Committee of Shenyang Women's and Children’s Hospital. The purpose of randomization is to eliminate selection bias.

**Fig. 1 Fig1:**
[figure not shown]
Trial design. pCR, pathological complete response

The trial will only include women with early-stage EC. The criteria for early-stage EC are: (1) stage 1 disease (absence of lymphadenopathy or pelvic masses); (2) endometrioid cell type and International Federation of Obstetrics and Gynecology (FIGO) grade 1 disease; (3) no evidence of lymph vascular space invasion on examination of curettage specimens; (4) absent or only minimal myometrial invasion (depth of infiltration < 1/2 muscle thickness on magnetic resonance imaging [MRI] to exclude deeply invasive cancers); (5) serum cancer antigen (CA)125 level ≤ 30 U/mL [31].

Through strict patient inclusion criteria, we expect to control the probability of disease progression in trial patients at 3%. All patients will receive examinations and laboratory and imaging studies at baseline and 3, 6, 9, 12, 18, and 24 months after starting treatment.

### Patients

Patients who meet the eligibility criteria below will be recruited from our clinic. Oral and written information about the study will be provided by the examining doctor.

### Eligibility criteria

#### Inclusion criteria

Females with a body mass index (BMI) > 24 kg/m^2^ who wish to maintain fertility.Aged over 18 years and under 45 years at the time of randomization.No contraindications to pregnancy.Histologically confirmed complex EHA or grade 1 EC on a curette or endometrial biopsy tissue specimen.Computed tomography (CT) of the pelvis, abdomen, and chest (or chest x-ray) indicates the absence of extrauterine disease.MRI shows less than 50% of myometrial invasion (women with EC only).No evidence of lymph vascular invasion on curetting specimens.FIGO stage IA EC.Serum CA 125 level ≤ 30 U/mL.No hypersensitivity or contraindications to LNG-IUD, MA, or metformin.Ability to comply with endometrial biopsies at specified intervals.No use of metformin for at least 2 years before study participation.No history of LNG-IUD use.No prior use of MAP.The primary physician recommended treatment with LNG-IU or MA for EHA or grade 1 EC.A negative pregnancy test within 7 days of starting treatment.Understanding the study design, risks and benefits, and providing informed consent.

#### Exclusion criteria

Patients who meet any of the exclusion criteria at baseline will be excluded.Eastern Cooperative Oncology Group (ECOG) performance status > 3.MRI shows grade 1 EC with myometrial invasion > 50%, grade 2 or grade 3 EC.Histological cell type other than EC (sarcoma or high-risk cell type, e.g., papillary serous or clear cell).Prior treatment for EC or EHA.A history of pelvic or abdominal radiotherapy.Renal impairment (creatinine > 150 µmol/L [1.7 mg/dL]), acute pulmonary edema, or liver failure.Unwilling to have additional endometrial biopsies, or unable to attend 3 monthly clinical assessments.Unable to provide informed consent or complete questionnaires.Medical imaging shows evidence of extrauterine spread.A congenital or acquired uterine anomaly which distorts the uterine cavity.Acute pelvic inflammatory disease.Concurrent with different cancer.Chronic (daily use for > 1 month) use of cimetidine (significant increase in metformin concentration and risk of lactic acidosis).Use of Iodinated contrast agents within the past 48 h (significant increase in metformin concentration and risk of lactic acidosis).Pregnant or lactating.History of hypersensitivity to metformin or discontinuation due to adverse effects.High risk of thrombosis.Surgery within a week before starting treatment.Current or history of cerebral and/or cardiac infarction or thrombophlebitis.Valvular heart disease, atrial fibrillation, endocarditis, or other serious cardiac conditions.Currently receiving hormone treatments.

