### Interventions

The LNG-IUD is approved for contraception, treatment of idiopathic menorrhagia, and prevention of endometrial hyperplasia. The most common adverse reactions are uterine/vaginal bleeding alterations, amenorrhea, intermenstrual bleeding and spotting, abdominal/pelvic pain, and ovarian cysts. The device is prohibited for use in women with known or suspected pregnancy, congenital abnormal uterine development, breast cancer, unexplained vaginal bleeding, reproductive tract infection, and other conditions.

Systemic progestogen therapy, such as MA 160 mg orally once a day, is effective for the treatment of hormone-sensitive hyperplasia and tumors [32]. However, PRs are often downregulated leading to a relatively short duration of effectiveness [33]. In addition, systemic therapy is associated with low compliance rates due to adverse effects including nausea, thromboembolic complications such as deep vein thrombosis (DVT), pulmonary embolism (PE), stroke, weight gain, abnormal vaginal bleeding, and increased risk of breast cancer [34].

Study participants will be instructed to take metformin with meals, 1000 mg daily. This dose is similar to that used in clinical trials as an adjuvant breast cancer treatment (NCT00909506 and NCT01302002), ranging from 500 to 1000 mg daily. Metformin is well-tolerated by the vast majority of patients with no significant side effects. The gastrointestinal adverse effects of metformin are dose-dependent [35]. The dose of 1000 mg daily can be reduced to 500 mg daily if needed. Metformin is associated with abdominal pain, diarrhea, lactic acidosis, nausea and vomiting, and taste changes [35]. Metformin decreases absorption of vitamins B9 and B12, in turn elevating homocysteine levels. Metformin is not used for patients with moderate or worse renal function impairment.

Because all participants in the trial will be obese, a weight loss program will be implemented. The weight loss program is an evidence-based and tested diet and exercise intervention program that has led to weight loss success in obses people [36]. Exercise levels (sedentary, moderately active, and sufficiently active) will be measured using the Active Australia Survey [37].

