### Criteria for discontinuation of trial treatment

The criteria for the discontinuation of a trial medication are as follows:A participant declines further participation or withdraws their consent.Cancelation of the entire study.The protocol treatment will be stopped if it does not result in remission according to the following criteria: no treatment response or pCR by 1 year; disease progression at any time; relapse after remission.Severe adverse events (progressive or persistent) which may be related to the medication (such as hemorrhagic shock due to massive vaginal bleeding, severe allergy, thrombosis, liver function damage) and newly diagnosed other malignancy (e.g., breast cancer) will be evaluated by 2 chief physicians before the trial is stopped.Any situation in which the LNG-IUD, MA, or metformin treatment cannot be continued according to the judgment of the physician.

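### If moderate renal impairment starts at eGFR 60, the creatinine exclusion of 150 µmol/L is looser than the protocol's own rule on metformin

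*Protocol article*

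**What the plan says.** Three statements in the protocol article bear on renal function and metformin.

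- Exclusion criteria: "Renal impairment (creatinine > 150 µmol/L [1.7 mg/dL]), acute pulmonary edema, or liver failure". This is the only renal limit in the article that carries a number.
- Interventions: "Metformin is not used for patients with moderate or worse renal function impairment". No creatinine or eGFR value is attached, and moderate is not defined.
- Inclusion criteria: "No hypersensitivity or contraindications to LNG-IUD, MA, or metformin". This item has no renal threshold either.

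Every participant is meant to take the drug. The abstract describes a "randomized, phase-II single-center trial of LNG-IUD plus metformin or megestrol acetate (MA) plus metformin", and the Interventions section sets the dose: "Study participants will be instructed to take metformin with meals, 1000 mg daily". The dose may be halved if needed. Entry requires an age over 18 and under 45 years, and "Females with a body mass index (BMI) > 24" kg/m².

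**The concern.** A single creatinine value corresponds to different levels of renal function depending on age, sex and body size. In young women, 150 µmol/L may already mean substantially reduced clearance. If so, the number that the recruiting doctor checks classes a woman as not renally impaired, while the metformin rule in Interventions says she should not have the drug. Neither allocation avoids it.

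What is at stake is safety at entry. The exclusion list itself treats metformin accumulation as a hazard: its cimetidine and iodinated contrast items both give raised metformin concentration and lactic acidosis as the reason. A renal limit that does not match the protocol's metformin rule sits badly beside those two items.

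**Working it through.** **Inputs from the protocol.** Creatinine limit 150 µmol/L (Exclusion criteria); women aged 19 to 44 in whole years and BMI above 24 (Inclusion criteria).

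**Assumptions not in the protocol.** The equations below, and the upper limit of moderate impairment. The main case is 60 mL/min/1.73 m² (moderate = 30 to 59); 45 and 30 are tried as alternatives.

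**Step 1. The protocol's own conversion.** 150/88.4 = 1.697 mg/dL, which agrees with the printed 1.7.

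**Step 2. eGFR at the printed limit.** With Scr = 1.697 mg/dL:

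- CKD-EPI 2021, female: 142 × (Scr/0.7)^-1.2 × 0.9938^age × 1.012
- CKD-EPI 2009, female: 144 × (Scr/0.7)^-1.209 × 0.993^age
- MDRD, female: 175 × Scr^-1.154 × age^-0.203 × 0.742

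| Age | CKD-EPI 2021 | CKD-EPI 2009 | MDRD |
|---|---|---|---|
| 19 | 44.1 | 43.2 | 38.8 |
| 25 | 42.5 | 41.4 | 36.7 |
| 35 | 39.9 | 38.6 | 34.3 |
| 44 | 37.8 | 36.2 | 32.7 |

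All values are below 60 and below 45; none is below 30.

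**Step 3. Creatinine at which each assumed limit is reached.** The equations are solved for Scr and multiplied by 88.4. For example, CKD-EPI 2021 gives Scr = 0.7 × (142 × 1.012 × 0.9938^age / limit)^(1/1.2). Results in µmol/L, age 19 to age 44:

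| Assumed limit | CKD-EPI 2021 | CKD-EPI 2009 | MDRD |
|---|---|---|---|
| 60 | 116 to 102 | 114 to 99 | 103 to 89 |
| 45 | 148 to 130 | 145 to 125 | 132 to 114 |
| 30 | 207 to 182 | 203 to 175 | 187 to 162 |

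With a limit of 60, women between roughly 89–116 and 150 µmol/L count as moderately impaired yet are not caught by the creatinine item. With a limit of 45 the band is narrower: at age 19 on CKD-EPI 2021 it is 148 against 150 µmol/L. With a limit of 30 there is no conflict.

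**Step 4. Sensitivity to body size.** Cockcroft-Gault, (140 − age) × kg × 0.85 / (72 × Scr), at 150 µmol/L and an assumed height of 160 cm, age 19 to age 44:

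- 61.7 kg (BMI 24.1, just above the entry limit): 51.9 to 41.2 mL/min
- 90 kg, actual weight: 75.8 to 60.1 mL/min
- 90 kg, adjusted weight of 67.4 kg (ideal weight plus 0.4 of the excess): 56.8 to 45.0 mL/min

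On actual weight, 60 mL/min is reached at 71.3 kg (BMI 27.8) at age 19 and at 89.8 kg (BMI 35.1) at age 44. With a limit of 60, the conflict therefore remains for lighter eligible women and disappears for heavier ones. With a limit of 45 it remains only for the lightest women aged about 35 or more: the weight giving 45 mL/min is 61.6 kg (BMI 24.1) at 35 and 67.4 kg (BMI 26.3) at 44.

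**The case against.** The strongest reply is that eligibility criteria apply together. A woman who passes the creatinine item must still have no contraindication to metformin. Read with the sentence in Interventions, that requirement excludes her. This stands. A reader might infer that the protocol permits metformin in moderately impaired women, and the documents do not support that. What the reply leaves untouched is that the inclusion item has no threshold, so it cannot correct the one number that is printed.

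A second reply is that moderate is undefined, so the conflict comes from an imported definition. This stands in part. A reader might infer that 150 µmol/L is too loose on any definition; Steps 3 and 4 show that it is not.

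A third reply is that the sentence in Interventions is general background and the creatinine figure is how the trial puts it into practice. That would reconcile the two only if moderate began at an eGFR no higher than about 33 to 44, depending on age and equation, or if clearance were judged by actual-weight Cockcroft-Gault in heavier women. The protocol says neither.

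A fourth reply is that the article is condensed and baseline assessments follow a trial operating procedure that is not shown. Renal grading may well be set there, and its absence from the article is not the complaint. The point concerns two printed statements that do not match on the usual reading.

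Finally, the physician may stop metformin during treatment under "Any situation in which the LNG-IUD, MA, or metformin treatment cannot be continued according to the judgment of the physician". That is a safeguard after entry and does not settle the entry number. Nothing is claimed here about safety testing during follow-up.

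**Conclusion.** The point holds conditionally and is minor. Taking moderate impairment as an eGFR of 30 to 59, the creatinine exclusion is looser than the metformin rule for every eligible age under CKD-EPI 2021, CKD-EPI 2009 and MDRD. The gap runs from about 89–116 µmol/L up to 150 µmol/L. The conclusion rests on that assumed definition and on the use of an eGFR equation.

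The defect is a screening number set at the wrong level, with the correct answer left to an item that has no threshold. The protocol does not give the number of women in the affected band; in this age range it is probably small. The pCR endpoint and its analysis are not affected.

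**What to change.** In the Exclusion criteria, replace the creatinine cut-off with a single baseline eGFR limit, name the equation, and set it to match the metformin rule in Interventions. For example, exclude an eGFR below 60 mL/min/1.73 m² if moderate means 30 to 59. The exact limit is for the sponsor's clinical team.

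This is a one-line amendment. The eGFR is calculated from the screening creatinine that the present criterion already needs, so it adds no test or visit. The downside is possibly a few more screening exclusions.

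The change should be confined to entry. Applying the same limit to continued metformin would need creatinine at follow-up visits, which Table 1 does not list, so it would not be free of cost and is not proposed here.

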### Study assessments and procedures

The study assessments and procedures performed at baseline and 3, 6, 9, 12, 18, and 24 months are summarized in Table 1.

**Table 1 Tab1:** Schedule of patient assessments

	Baseline	Day 1	3 months (± 14 days)	6 months (± 14 days)	9 months (± 14 days)	12 months (± 14 days)	18 months (± 14 days)	24 months (± 14 days)
Assessment								
Informed consent	√							
CT of pelvis/abdomen^a^	√			√		√	√	√
CT chest (or chest X-ray)	√			√		√	√	√
MRI of pelvis	√			√		√	√	√
Pelvic ultrasonography^b^	√		√	√	√	√	√	√
CA125	√		√	√	√	√	√	√
FBG (fasting blood-glucose)	√		√	√	√	√	√	√
Serum or urine pregnancy test	√	√(urine)						
Fasting blood sugar	√		√	√	√	√	√	√
HbA1c	√		√	√	√	√	√	√
HE4 (human epididymal protein4)	√		√	√	√	√	√	√
Blood collection for biomarkers and genetic testing	√							
ERα, PRα and PRβ (estrogen receptor, progesterone receptor)								
Medical history	√							
Concomitant medications	√		√	√	√	√	√	√
ECOG	√		√	√	√	√	√	√
Height	√							
Weight	√		√	√	√	√	√	√
BMI	√		√	√	√	√	√	√
Surgical, medical, gynecologic, and family history	√							
Self-efficacy and social support questionnaire	√		√	√	√	√	√	√
Adverse events			√	√	√	√	√	√
Hysteroscopy, D&C			√	√	√	√	√	√
Intervention adherence			√	√	√	√	√	√

*BMI* body mass index, *CA125* cancer antigen 125, *CT* computed tomography, *D&C* dilation and curettage, *ECOG* Eastern Cooperative Oncology Group, *HbA1c* glycosylated hemoglobin, *MRI* magnetic resonance imaging

^a^CT scans will be performed every 6 months. However, if the ultrasound shows obvious lesions in the uterine cavity and tissue pathological examination indicates no remission or the disease has progressed, additional CT examination will be performed

^b^Patients will receive pelvic ultrasonography and hysteroscopic and curettage every 3 months for endometrial pathological examination. If the ultrasound shows obvious lesions in the uterine cavity and tissue pathological examination indicates no remission or the disease has progressed, additional CT/MRI examination will be performed

